#### *Local control at 3 years of treatment*

Local control will be defined by :

- the non-progression of PSA according to the Phoenix criteria after obtaining the nadir,

- a non-progressive clinical exam (digital rectal exam),

- and the absence of pathologic signal with MRI.

#### *Global survival*

Time between :

- inclusion date,
- date of death, whatever the cause,
- Patients alive at the time of the analysis will be censored at the date of the last follow-up visit.

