| **INCLUSION CRITERIA** | - Prostate Adenocarcinoma, histologically proven - With at least one of the following criteria : - T2b - and/or PSA between 10 and 20 ng/ml - and/or Gleason Score equal to 7 - Prostate volume ≤ 80 cc - Absence of lymph node involvement (adenopathy < 1.5 cm on scanner or MRI, and/or negative lymph node dissection) - Absence of metastasis (bone scintigraphy) - Age  18 years - Absence of previous pelvic irradiation - Absence of previous antitumoral treatment, including prostatectomy and/or hormonotherapy - Good general condition: ECOG  1 (appendix 3) - Absence of contraindication to the placement of fiducial markers – hemostasis problems shall be corrected before implantation - Life expectancy greater or equal to 10 weeks - Patient affiliated with a health insurance system - Patient having signed the informed consent |
| EXCLUSION CRITERIA | - Absence of histological proof - Unfavorable stage (T2c and/or PSA > 20 ng/ml and/or Gleason > 7) - Favorable stage (T1c T2a and PSA < 10 ng/ml and Gleason < 7) - Prior history of uncontrolled cancer and/or treated for less than 5 years (except basocellular skin cancer) - Contraindication to MRI - IPSS score >10 - Recurrent or metastatic disease - Known gold allergy - Patient already included in another therapeutic trial of an experimental drug - Unavailability to medical follow-up for geographical, social or psychological reasons |
| **NUMBER OF PATIENTS** | 76 patients receiving hypofractionated stereotactic boost irradiation :  - 38 by CyberKnife  - 38 by linear accelerator |
| **STUDY DURATION** | Start of the study: September 2009  End of enrollment: September 2012  End of study: December 2015 |

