| **ASSESSMENT CRITERIA** | Primary  Urinary or rectal toxicity: According to the NCI-CTCAE v3.0 rating scale (appendix 10). Acute toxicities are defined as all toxicities occurring in the 6 months following the start of radiotherapy. Late toxicities are defined as all toxicities occurring beyond 6 months.  **Secondary**   - Rate of local control at 3 years: non progression of : - PSA level according to the Phoenix definition (nadir to be obtained) - Clinical examination (rectal touch) - No pathological signal on MRI - Median time without progression for the entire cohort: interval between the date of inclusion and the date of progression, whether clinical (rectal touch) or radiological (prostatic MRI). - Median overall survival: Median time for the entire cohort comprising the time between the date of inclusion and the date of death, whatever the cause. - Survival without biological failure at 3 years: Phoenix criteria for PSA increase (nadir + 2 ng/ml) (see chapter 6.7.3) - Technical criteria: Implantation of markers, treatment time, cumulative dosimetry, administration and length of boost session - PSA kinetics during the entire treatment (between the two irradiation phases) and after treatment - Sexual dysfunction = international questionnaire IIEF 5 - Urinary discomfort = IPSS questionnaire |
| **STATISTICAL ANALYSIS** | The initial characteristics of included patients will be presented in the form of summary tables. Continuous variables will be summarized by conventional descriptive statistics parameters (median and outlying  values, mean and standard deviation when necessary). Category variables will be presented in the form of contingency tables (absolute frequency and percentage of each modality), additionally stating the number of missing data, along with the 95% confidence interval.  Subject inclusion and exclusion criteria will be checked against data entered into the case report forms when possible. Any deviations from the protocol will be documented.  Survival will be analyzed by the Kaplan-Meier nonparametric method. |

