### 6.6.4 Follow-up visit

Evaluation will be done 6, 9, 12, 18, 24 and 30 months after the last radiotherapy session :

 Clinical examination

- Weight, performance status or ECOG (appendix 3)
- Digital rectal exam
- Evaluation of late toxicity associated with irradiation

 Blood tests

- Tumor marker: PSA

 Paraclinic examinations

- Prostate and pelvis MRI (at 6, 12 and 24 month)

 Questionnaires

- Sexual quality of life “IIEF-5” (appendix 11)

- Urinary discomfort “IPSS” (appendix 12)

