### 6.6.5 End of study evaluation

Evaluation will be done 36 months after the last radiotherapy session or at premature end from the study (see chapter 6.5).

 Clinical examination

- Weight, performance status or ECOG (appendix 3)
- Digital rectal exam
- Evaluation of late toxicity associated with irradiation

 Blood tests

- Tumor marker: PSA

 Laboratory and special studies/tests

- Prostate and pelvis MRI

 Questionnaires

- Sexual quality of life “IIEF-5” (appendix 11)

- Urinary difficulty “IPSS” (appendix 12)

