### 6.6.6 Long term evaluation

Long term evaluation will be identical to the follow-up evaluation (see chapter 6.6.4) and will be done 48 and 60 months after the last radiotherapy session.

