### 6.8.2 Statistical analysis

The initial characteristics of included patients will be presented in the form of summary tables. Continuous variables will be summarized by conventional descriptive statistics parameters (median and outlying values, mean and standard deviation when necessary). Category variables will be presented in the form of contingency tables (absolute frequency and percentage of each modality), additionally stating the number of missing data, along with the 95% confidence interval.

Subject inclusion and exclusion criteria will be checked against data entered into the case report forms when possible. Any deviations from the protocol will be documented.

Survival will be analyzed by the Kaplan-Meier nonparametric method.

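### Overall survival dates deaths exactly but censors living men back at their last visit, so the Kaplan-Meier curve is distorted beyond 36 months and the planned median can be an artefact

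*Protocol*

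**What the plan says.** Protocol 6.7.2 (Global survival) measures time from inclusion to "date of death, whatever the cause". For the others it says "Patients alive at the time of the analysis will be censored at the date of the last follow-up visit".

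The visit schedule is in three places:
- 6.6.3 and 6.6.4: a visit at 3 months, then "Evaluation will be done 6, 9, 12, 18, 24 and 30 months after the last radiotherapy session".
- 6.6.5: "Evaluation will be done 36 months after the last radiotherapy session or at premature end from the study".
- 6.6.6: long-term evaluation "will be done 48 and 60 months after the last radiotherapy session". Nothing is scheduled after 60 months.

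On analysis, 6.8.2 says "Survival will be analyzed by the Kaplan-Meier nonparametric method". The Synopsis names the summary: "Median overall survival: Median time for the entire cohort".

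The Synopsis also gives the calendar: "Start of the study: September 2009", enrollment closing in September 2012 and the study ending in December 2015.

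**The concern.** Kaplan-Meier needs censoring that carries no information about the outcome. Here, two men who have both passed their 36-month visit are treated differently according to what happens next. The one who dies at month 45 contributes exposure to month 45 and an event. The one known to be alive at month 45, when the analysis is made, is cut back to his 36-month visit. Deaths are then divided by a risk set from which survivors were removed because they survived.

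Up to 36 months visits are 3 to 6 months apart and every man has later follow-up, so nothing is lost. Beyond that, up to 12 months of known survival is discarded per man. After the last planned visit all of it is discarded. The stated summary is a median, which is read from exactly that part of the curve.

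**Working it through.** **The plan's own figure.** The protocol gives no death rate, precision or power for overall survival. Its one computed figure is the Fleming sample size in 6.8.3 (85% versus 95%, 5% error, 90% power). It reproduces: 75.1, rounded up to 76, and the rule of at least 70 of 76 has exact error 0.0497 and power 0.914. The survival rule does not touch it.

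**Inputs from the protocol.** Counting from September 2009, enrollment closes at month 36 and the study ends at month 75. Potential follow-up therefore runs from 75 − 36 = 39 to 75 months. There are 76 men, with visits as listed above.

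**Assumptions.** Analysis at month 75; uniform accrual; last radiotherapy about 2 months after inclusion, which puts the late visits at 38, 50 and 62 months from inclusion; full attendance; all deaths known; constant mortality r of 1, 2 or 3% per year.

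**Who is moved back.** Of the men alive at analysis:
- Follow-up 39–50 months: share 11/36, censored at 38.
- Follow-up 50–62 months: share 12/36, censored at 50.
- Follow-up 62–75 months: share 13/36, censored at 62.

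**Approximate size by hand.** The hazard is inflated by (exposure discarded) ÷ (exposure kept):
- Months 38–48: mean discarded (9 × 5.5 + 2 × 10)/11 = 6.32 months; (11 × 6.32)/(25 × 10) = 0.278.
- Months 38–50: mean discarded 6.5 months; (11 × 6.5)/(25 × 12) = 0.238.
- Months 50–60: mean discarded (10 × 5 + 2 × 10)/12 = 5.83 months; (12 × 5.83)/(13 × 10) = 0.538.

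Excess cumulative hazard at 48 months is r × 0.278 × 10/12 = 0.232r. At 60 months it is r × (0.238 + 0.538 × 10/12) = 0.687r. Multiplying by true survival exp(−rt) gives a downward bias of about 0.2 / 0.4 / 0.6 points at 48 months and 0.7 / 1.2 / 1.8 points at 60 months, for r = 1 / 2 / 3%.

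**Simulation** (4,000 trials of 76 men per rate), survival in %:

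| Months from inclusion | Last-visit rule (1 / 2 / 3%) | Common cut-off (1 / 2 / 3%) | SD with common cut-off, points |
|---|---|---|---|
| 36 | 97.1 / 94.1 / 91.4 | 97.1 / 94.1 / 91.4 | 1.9–3.2 |
| 48 | 95.8 / 91.9 / 88.2 | 96.1 / 92.3 / 88.8 | 2.2–3.6 |
| 60 | 94.5 / 89.3 / 84.5 | 95.2 / 90.5 / 86.2 | 2.6–4.4 |
| 72 | 82.9 / 67.9 / 58.7 | 94.2 / 88.6 / 83.6 | 3.7–6.1 |

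Independent repeats and the hand calculation together span 0.2–0.7 points at 48 months and 0.6–1.8 points at 60.

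**The median.** After month 62 every living man has been censored, so the risk set holds only men who will die before the cut-off. The curve must then fall to zero at the last such death. A false median therefore needs just one known death after month 62. Exposure there is 76 × 13/36 × 6.5/12 = 14.9 person-years. Expected deaths are 14.9 × r × exp(−62r/12) = 0.141 / 0.268 / 0.382, and the chance of at least one, 1 − exp(−expected), is 13.2 / 23.5 / 31.7%. The simulation gives 13 / 25 / 32%, against under 1% with a common cut-off.

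**Later analysis.** At month 99 every man has passed the 60-month visit and there is no bias through 60 months. The tail is worse: at 72 months the rule shows 64 / 53 / 46%, and a false median appears in 68 / 88 / 96% of trials.

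**Incomplete death capture.** With half of all deaths known, r = 2% and a cut-off at month 75, the rule gives 95.8% at 48 months and 94.5% at 60, against true values of 92.3% and 90.5%. The sign has reversed.

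**The case against.** A reader might infer that survival after 36 months is bound to look worse than it is. The documents do not support that without a condition. Section 6.5 lists death as a reason for leaving the study but sets up no death reporting between visits. Under 6.7.1, later serious adverse events must be declared only if reasonably related to treatment or the research. Appendix 2 labels 36 months as exit from the study. An unrelated death between annual visits has no assured route into the database, and the half-capture result shows that the estimate can then be too high. This part of the objection stands: the direction is conditional.

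It also stands that the shift through 60 months is smaller than the sampling error, that it vanishes there if analysis waits until everyone has passed the 60-month visit, and that the mortality rates are assumed. A reader might further infer that the remedy is free. It is not quite: a date last known alive taken from incidental contacts still lags behind exactly dated deaths and removes only part of the bias, so the full gain needs a vital-status check.

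What does not stand is that this belongs to the analysis plan, or that a shift of 1 or 2 points cannot move a median. A cut-off date may well be left to the SAP, but the unequal rule is written in the protocol. It speaks of men alive at the time of the analysis, so it presupposes that their status is known and then sets it aside. The median is exposed through the tail, not through the 60-month shift.

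**Conclusion.** The rule makes censoring depend on outcome, and Kaplan-Meier does not allow for that. With deaths between visits known, a December 2015 cut-off and 1 to 3% annual mortality, the bias is nil at 36 months, small at 48 and 60 months, and large past the last planned visit: 11 to 25 points at 72 months. There the planned median can be reached by artefact in roughly one trial in eight to one in three. With deaths only partly captured, the 48- and 60-month figures can err upward instead.

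This is a minor point. Overall survival is a secondary, descriptive criterion with no threshold. It would be wrong to read the finding as casting doubt on the toxicity endpoint, the 76 patients or the 70-of-76 rule, none of which uses this censoring.

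**What to change.** Replace the censoring line in 6.7.2 with a symmetric rule. Set one data cut-off date, check the vital status of every man at that date, and count deaths up to it. Censor men confirmed alive at the cut-off, and any whose status cannot be confirmed at the date last known alive. The cost is a small vital-status check across the 8 centers, with no extra patients or visits.

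A free alternative is to end the overall-survival curve at the 36-month visit for deaths and censoring alike. On the protocol's dates all men should just reach it. Assessment, first phase, gap and boost take at most 21 + 42 + 10 + 9 = 82 days, about 2.7 months, and 36 + 2.7 = 38.7 against a minimum of 39 months; any postponement would use up that slack. Under this option survival at 36 months replaces the median, which would not be reached at the mortality assumed here. It still relies on deaths before that visit being recorded.

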#### *Survival without metastatic disease*

Time between:

- inclusion date,
- date of appearance of the first metastasis.

### 6.7.3 Evaluation of biological response

The Prostate Specific Antigen (or PSA) is sufficiently specific of prostate adenocarcinoma. The biological response will be evaluated according to the progression of PSA, measured at each monitoring visit.

Biological progression is defined as:

- according to the Phoenix definition, biological progression is defined as an increase in the total PSA serum level + 2 ng/ml above the nadir

- Recommendation : in case of PSA elevation of less than nadir + 3 ng/ml, it is not recommended to plan a specific salvage therapy (Phoenix expert panel consensus [Roach 2006])

- In case of death, the patient is considered in biological remission if a PSA increase has not been confirmed by three successive measures.

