## 7.5 Subsequent antitumor treatments

In case of tumor progression, the patient will benefit from all treatments relevant to his situation. The patient presenting with distant progression remains in the study. Follow-up will be observed.

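### Biological failure rests on PSA nadir + 2 alone, so a man who starts PSA-lowering salvage treatment before that level is scored failure-free or censored, and either reading flatters the 3-year rate

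*Protocol*

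**What the plan says.** Section 6.7.3 of the protocol gives one criterion: "biological progression is defined as an increase in the total PSA serum level + 2 ng/ml above the nadir". The synopsis names survival without biological failure at 3 years as a secondary criterion with the same threshold and refers back to section 6.7.3.

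Section 6.7.3 mentions salvage treatment only as advice: "in case of PSA elevation of less than nadir + 3 ng/ml, it is not recommended to plan a specific salvage therapy". It does not say how a man who has started such treatment is to be counted.

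Section 7.5 covers treatment after progression: "In case of tumor progression, the patient will benefit from all treatments relevant to his situation". It adds: "The patient presenting with distant progression remains in the study". Section 6.5, by contrast, lists disease progression among the reasons for which termination from the study must take place, and section 6.6.5 then places the final evaluation, including PSA, at that premature end.

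Section 6.8.2 names Kaplan-Meier for survival and gives no censoring rule for salvage treatment.

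**The concern.** PSA measures the effect of the radiotherapy only while nothing else is lowering it. Once a man starts a treatment that suppresses PSA, later values no longer show whether the boost controlled his disease. A definition that looks only at nadir + 2 treats his low PSA as a success, although the treatment was started because the disease had progressed.

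The trial has a single treatment strategy and no randomised comparator, so the 3-year rate will be read on its own and no control group would share the same bias. Section 4.3.5 of the protocol uses PSA decrease as an indirect indicator of the ablative effect of the irradiation. A favourable bias in the PSA endpoint therefore bears on a conclusion the trial wants to draw.

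**Working it through.** **1. Can salvage start before nadir + 2?** Rectal examination is scheduled at every post-treatment visit (sections 6.6.3 to 6.6.6). Prostate and pelvis MRI is scheduled at 3, 6, 12, 24 and 36 months (sections 6.6.3 to 6.6.5), and bone scan when clinically indicated (Appendix 2). Each can show progression without reference to PSA, and section 7.5 then allows treatment. The nadir + 3 advice does not close this route: it is a recommendation and concerns PSA elevation, not treatment for clinical, MRI or distant progression.

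**2. The definition applied to invented values.** Take a nadir of 0.6 ng/ml, so the failure level is 0.6 + 2 = 2.6.

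| Man | Course | Result by the text of 6.7.3 |
| --- | --- | --- |
| A | PSA 2.0 at 24 months (rise 1.4) with bone progression; PSA-lowering treatment started; PSA below 0.1 at 30 and 36 months; follow-up continues (7.5) | Never reaches 2.6; free of biological failure at 3 years |
| B | Same as A, but participation ends at progression (6.5) | Last PSA 2.0, no event; censored at about 24 months |
| C | PSA 2.6 at 24 months, no other sign of progression | Failure at 24 months |
| D | PSA 3.6 (nadir + 3), then salvage | Already an event; a later fall does not undo it in Kaplan-Meier |

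Men A and B have progressed, yet both are scored more favourably than man C. In man A the suppressed value would also become the new nadir, so any later failure would be dated to a rise after salvage rather than to 24 months.

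**3. Denominator.** The protocol gives no expected rate or power for this endpoint. Its only sample-size figure is the 76 evaluable patients for the toxicity endpoint (section 6.8.3). It reproduces with p0 = 0.85, p1 = 0.95, one-sided alpha 5% and power 90%:

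n = [(1.645 × √(0.85 × 0.15) + 1.282 × √(0.95 × 0.05)) / 0.10]² = 75.1, rounded up to 76.

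The exact binomial properties of the rule of at least 70 out of 76 are alpha 0.0497 and power 0.914. This figure is sound and serves here only as the denominator.

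**4. Shift per man.** With complete 3-year follow-up of 76 men, scoring one such man failure-free instead of failed moves the proportion by 1/76 = 1.3 points.

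**5. Illustration.** Assume 8 men reach nadir + 2 and k further men start salvage before it. Both counts are assumptions. Leaving the k men out is a rough stand-in for censoring them.

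| k | Salvage ignored: 68/76 | k men left out: (68 − k)/(76 − k) | Salvage counted as failure: (68 − k)/76 |
| --- | --- | --- | --- |
| 1 | 89.5% | 89.3% | 88.2% |
| 2 | 89.5% | 89.2% | 86.8% |
| 3 | 89.5% | 89.0% | 85.5% |
| 5 | 89.5% | 88.7% | 82.9% |

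Both of the first two readings lie above the last for every k. Censoring removes little of the gap, because it assumes that a man who leaves at progression has the same later risk as the men who remain.

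**The case against.** The strongest case against is that the protocol nowhere says a salvaged man counts as controlled. It is silent on salvage, and censoring or event rules are commonly left to a statistical analysis plan, which is not at hand. Part of this stands: such a plan could add a rule. But the protocol does more than leave a detail open. It states the event, and that event carried out as written gives the favourable result. A later rule would have to alter the definition in 6.7.3.

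A second objection is that section 6.5 takes men out at progression, so PSA values at 30 and 36 months would not be study data. That is a fair reading, and it conflicts with 7.5, which keeps men with distant progression in. The schedule in Appendix 2 adds to the doubt, since its footnote waives MRI after earlier tumour progression as though visits go on. The conflict does not rescue the endpoint, because exit at progression turns a favourable score into favourable censoring.

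Several stronger readings are tempting, and the documents do not support them:

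- A reader might infer that any man with salvage-suppressed PSA is counted as controlled. Men treated in line with the nadir + 3 advice have already passed nadir + 2 and remain events. The separate rule for deaths ("the patient is considered in biological remission if a PSA increase has not been confirmed by three successive measures") could blur this for a man who dies, but that case is narrow and the point does not depend on it.
- A reader might extend the bias to local control. Section 6.7.2 also requires a non-progressive rectal examination and no pathologic MRI signal, so a man with either finding already fails. Counting salvage there would turn a man treated for distant disease with a clear prostate into a local failure.
- A reader might suppose that hormonotherapy was left out to keep PSA interpretable. Section 4.3.5 gives lack of benefit after high radiation doses as the reason.

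**Conclusion.** The point holds in a limited form. The definition in 6.7.3 ignores PSA-lowering salvage treatment started before nadir + 2. Such a man is either scored failure-free or censored at progression, depending on whether 7.5 or 6.5 governs, and both readings push the 3-year estimate in the boost's favour. Scored failure-free, each affected man adds about 1.3 points (1/76, assuming complete 3-year follow-up of 76 men).

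The number of such men cannot be derived from the protocol, so no total bias can be stated; the table above shows assumed counts only. This is a secondary endpoint without a hypothesis or power calculation. The toxicity decision rule and the 76 patients are untouched. The change is worth making because the error runs in one direction and is cheap to prevent.

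**What to change.** Add to section 6.7.3, for the survival-without-biological-failure endpoint only: the start of any salvage antitumour treatment before PSA reaches nadir + 2 counts as biological failure on its start date, and the nadir is determined only from PSA values before such treatment. Do not apply this rule to local control.

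Record the start date of subsequent antitumour treatment in the CRF. Section 7.5 does not expressly ask for it, and the schedule in Appendix 2 has no item for it.

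Reconcile section 6.5 with section 7.5 on follow-up after progression, so that it is clear which PSA values after progression are study data.

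The cost is a short addition to 6.7.3, one CRF item and a possibly slightly less favourable 3-year rate. The counting rule leaves treatment, visits and sample size as they are.

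### Section 6.7.3 sets a stricter PSA test for patients who die than for those who live, so biological failure depends on vital status

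*Protocol*

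**What the plan says.** Section 6.7.3 of the protocol gives two rules for the same outcome.

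- The definition: "according to the Phoenix definition, biological progression is defined as an increase in the total PSA serum level + 2 ng/ml above the nadir". No repeat measurement is required.
- The rule for patients who die: "In case of death, the patient is considered in biological remission if a PSA increase has not been confirmed by three successive measures".

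The synopsis defines survival without biological failure at 3 years by the Phoenix criterion (nadir + 2 ng/ml) and refers to section 6.7.3 for detail. Local control at 3 years, in section 6.7.2, has a PSA component worded as "the non-progression of PSA according to the Phoenix criteria after obtaining the nadir", with no reference to 6.7.3.

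PSA is measured 3 months after the last session (section 6.6.3). For later visits, section 6.6.4 says: "Evaluation will be done 6, 9, 12, 18, 24 and 30 months after the last radiotherapy session". A further evaluation comes at 36 months (section 6.6.5), then at 48 and 60 months (section 6.6.6). Section 6.8.2 says that survival will be analysed by the Kaplan-Meier method.

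**The concern.** An outcome definition should classify the same PSA series in the same way whoever it belongs to. Here the classification turns on whether the patient later dies. The stricter test falls only on patients who die, and it can only remove failures, never add them.

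This is more than detail left for a statistical analysis plan. The protocol states the rule. A plan that applied nadir + 2 to everyone would depart from the sentence on death, and a plan that followed that sentence would depart from the stated Phoenix definition. Two analysts could report different 3-year rates from the same data, each citing section 6.7.3.

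The word remission adds a second problem. It is neither an event nor a censoring rule, so it does not tell a Kaplan-Meier analysis what to do with the patient. Section 6.7.2, by contrast, states the event and the censoring for overall survival.

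**Working it through.** **1. The plan's own figures.** The protocol states no expected rate of biological control, so there is none to reproduce. Its one design calculation concerns toxicity (section 6.8.3: P0 = 85%, P1 = 95%, 5% and 10% error rates). With one-sided 5%, n = [1.645 × √(0.85 × 0.15) + 1.282 × √(0.95 × 0.05)]² / 0.10² = 75.1, rounded up to 76. Success at 70 or more of 76 has exact type I error 0.0497 and power 0.914. None of this uses PSA.

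**2. The two rules side by side.**

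| PSA history | Alive | Died |
| --- | --- | --- |
| Nadir + 2 never reached, no increase confirmed on three measures | No failure | Remission |
| Nadir + 2 reached, increase seen on one or two measures | Failure | Remission |
| Nadir + 2 reached, increase confirmed on three successive measures | Failure | Not covered by the remission sentence; failure under nadir + 2 |

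Only the middle row conflicts, and there the change is always from failure to remission. In a Kaplan-Meier analysis, turning an event into a later censoring removes a downward step, so the estimate can only rise.

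**3. How long three measures take.** On the scheduled visits (months 3, 6, 9, 12, 18, 24, 30, 36):

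| First measure | Third measure | Span (months) |
| --- | --- | --- |
| 3 | 9 | 6 |
| 6 | 12 | 6 |
| 9 | 18 | 9 |
| 12 | 24 | 12 |
| 18 | 30 | 12 |
| 24 | 36 | 12 |

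A first rise at month 30 has its third scheduled measure at month 48 (30, 36, 48), after the 3-year time point.

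**4. Size under assumed rates.** Neither rate is in the protocol. Assume 3-year biological failure b of 5-15%, 3-year death d of 2-10%, constant hazards and independence. Then h_b = −ln(1 − b)/3 and h_d = −ln(1 − d)/3. Treat every death within 12 months of failure, and within 3 years, as unconfirmed:

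P = ∫₀³ h_b · exp[−(h_b + h_d)t] · {1 − exp[−h_d · min(1, 3 − t)]} dt

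| b | d | P (%) | Expected patients in 76 |
| --- | --- | --- | --- |
| 5% | 2% | 0.028 | 0.02 |
| 10% | 5% | 0.139 | 0.11 |
| 15% | 10% | 0.419 | 0.32 |

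At the top of the range, h_b = 0.0542 and h_d = 0.0351, and 76 × 0.00419 = 0.32. The range is therefore 0.02 to 0.32 patients, or 0.03 to 0.42 percentage points.

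**5. Handling of death without PSA failure.** With the same hazards, b = 10% and d = 5%, the 3-year figure is 90.0% if such deaths are censored, 90.25% if they are held in remission to 3 years, and 85.5% if death is an event. Over the whole assumed range, holding them in remission instead of censoring adds 0.05 to 0.74 points. The protocol does not say which is meant.

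**The case against.** Several points on the other side have force.

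- **The sentence may have a narrower purpose.** It speaks of a PSA increase, not of biological progression, and may have been written for deaths with a PSA rising but still below the threshold. On that reading nobody is reclassified. The text does not limit itself in this way, so this supports rewording it and does not remove the conflict.
- **Measures are not rises.** A reader might infer that three successive rises are needed. The text says three measures, which could also mean one increase seen three times. Either is stricter than nadir + 2.
- **A fixed gain per patient is too simple.** It is tempting to say that each reclassified patient adds 1/76 = 1.3 points. That is a crude proportion. In a Kaplan-Meier estimate the step depends on the number at risk.
- **Deaths need not become successes.** Patients in remission at death may simply be censored then. The protocol does not say that they count as controlled to 3 years.
- **The 6-to-12-month window is not firm.** Section 6.7.5 speaks of quarterly PSA after treatment, which would make three measures span 6 months throughout. The visit sections and Appendix 2 give 6-monthly visits from month 12 to month 36.
- **Local control.** A reader might infer that it is biased too. Its definition does not cite section 6.7.3, so this holds only if its Phoenix component is meant to follow that section.
- **Estimand preferences.** Whether death is an event, a censoring or a competing event is a choice commonly made in the analysis plan. Its absence alone would be no finding.

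These points limit the size and reach of the concern. The asymmetry remains.

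**Conclusion.** The point holds as an internal contradiction in section 6.7.3. Classification of a secondary endpoint depends on vital status, and any resulting bias in survival without biological failure at 3 years is upward.

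The documents do not support a claim of material inflation. Under the assumed rates, well under one patient in 76 would be reclassified (0.02 to 0.32 patients; 0.03 to 0.42 points). That rests on constant hazards, on death being independent of PSA failure, and on counting only deaths within 3 years and within 12 months of failure. The number would be larger if deaths cluster after PSA failure, or if deaths after month 36 also reclassify earlier failures.

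The primary toxicity test and its rule of 70 in 76 are untouched. The case for change is that the rule is wrong as written and easily corrected.

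**What to change.** In section 6.7.3, remove the three-measure condition for patients who die. State that nadir + 2 ng/ml applies to every patient whatever the vital status, with failure dated at the first qualifying PSA.

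Replace the remission wording with one explicit rule for death without prior PSA failure in the Kaplan-Meier analysis: either an event or a censoring at death. The choice should agree with the endpoint's name. If death is censored, a name such as freedom from biological failure would fit better. A competing-risk analysis is optional. Also state whether the PSA component of local control follows section 6.7.3.

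The cost is a few lines of protocol text and the matching analysis code. No new data are needed and the sample size does not change. The reported rate may be slightly lower, or lower by more if death is made an event.
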